**Measures**

**3Tesla MRI:**

University of Bristol Clinical Research Imaging Centre (CRIC) [www.bristol.ac.uk/cricbristol](http://www.bristol.ac.uk/cricbristol)

*Summary Brain Imaging Protocol ~ 45min***.**

1. Anatomy / Volume
2. T1 FLAIR (Evidence of burden and pattern of vascular disease)
3. Diffusion Tensor Imaging (micro structure / evidence of recent ischaemia)
4. Resting Functional Imaging (marker of cerebral activity)
5. T2 Susceptibility weighted imaging (cerebral micro-bleeds)
6. Arterial Spin Labelling (measure of regional tissue perfusion

*Summary Cardiac Imaging Protocol ~ 20min*

1. Non-invasive imaging including fast gradient-echo cine images of the left and right ventricles.

**Aortic Stiffness :**

Carotid-femoral pulse wave velocity, augmentation index and central pressures.

Subjects will be studied after an overnight fast and 6 hours after abstinence from caffeine, tobacco, and inhaled short-acting β2 agonists. Therefore this assessment cannot be made on the same day as when consent is taken, but on a subsequent study visit. All tests are to be performed after 10 minutes of supine rest. After peripheral blood pressure is measured, radial artery waveforms are recorded with a high-fidelity micromanometer (Millar Instruments, Houston, TX). Pulse wave analysis (Sphygmocor; AtCor Medical, Sydney, Australia) will be used to generate a corresponding central waveform, using a validated transfer function . With the integral software, Augmentation Index will be calculated as the difference between the second and first systolic peaks as a percentage of pulse pressure. Aortic Pulse Wave Velocity (PWV) will be measured with the same device by sequentially recording ECG-gated carotid and femoral artery waveforms. Wave transit time will be calculated by the system software, using the R wave of a simultaneously recorded ECG as a reference frame. Aortic PWV was determined by dividing the distance between the two recording sites by the wave transit time .

**Retinal Photography:**

Non-mydratic, macular focused retinal photography will be collected by qualified technicians with the study site department of medical illustration. Generalised retinal arteriolar narrowing will be estimated by measuring retinal vessel diameters from photographs by use of validated imaging software. Reproducibility from photographs is excellent (kappa 0.80 – 0.99) (22).

**Renal Function:**

Serum, estimated Glomerular Filtration Rate (eGFR). Urine dipstick for microalbuminuria. Urine albumin creatinine ratio.

**Cognition Assessment:**

Montreal Cognitive Assessment (MoCA) is a well validated clinical tool used to assess all major cognitive domains. It will be administered by an appropriately trained study co-ordinator as per developer protocol and completed during the study visit.

**Other demographic and disease severity measures:**

1) Detailed medical history

2) Arterialised earlobe capillary or radial artery blood gases whilst breathing room air

3) Blood pressure in resting state x 3

4) Vital signs including Oxygen saturation, Heart Rate, Respiratory rate

5) Health Status Questionnaire - COPD Assessment Test (CAT) .

6) Mood Questionnaire - Hospital Anxiety & Depression (HAD) questionnaire .

9) Spirometry: ATS/ ERS guidelines

10) Snellen chart (visual acuity)

11) Blood tests: Full Blood Count, Urea and Electrolytes, Fasting Glucose and Lipids

**Management of Biological Samples:**

Routine serum samples will be collected in EDTA and SSC vacutainers during study visit 2 prior to vascular ultrasound. Study investigators will process clinical samples through the study site general pathology services. Immediately after being centrifuged, anonymised samples will be storage in a dedicated 80 degrees centigrade freezer at North Bristol NHS. This location has restricted access to trial research staff and approved lab staff only. The freezers are protected by a failsafe mechanism which ensures sample integrity by alerting staff in the event of failure.

**4. PARTICIPANT ENTRY**

Recruitment will be from inpatients and outpatient respiratory clinics at University Teaching Hospitals. An age-matched control group will be recruited from the local community either through local press advertisements or University non-healthcare staff. Controls will be excluded if they have any physician-diagnosed respiratory disease or self-reported memory difficulties.

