There is a high prevalence of traditional cardiovascular risk factors in patients with COPD including smoking, reduced physical activity and low socio-economic status. However, numerous studies have shown that airflow limitation is an independent risk factor for cardiovascular disease . Patients with COPD are at a significantly increased risk of cardiac events and stroke particularly in early disease and it is cardiovascular, not respiratory disease that is the leading cause of death . This evidence points to a potential 'COPD specific effect' that contributes to the increased vascular comorbidities.

Arterial stiffness is a non-invasive measure of vascular function and accurately predicts cardiovascular and cerebrovascular events. In addition, arterial stiffness is thought to contribute directly to end-organ vascular damage through reduced vessel compliance, excessive pressure pulsatility resulting in vascular remodelling and impaired blood flow . There is evidence of increased aortic stiffness in COPD, independent of smoking, which also relates to degree of airflow limitation and percent emphysema on thoracic CT . It has been suggested that arterial stiffness in COPD may be due to increased susceptibility to degradation of connective tissue or accelerated aging. These factors are also implicated in the development of emphysema suggesting a potential shared pathophysiology between pulmonary and vascular disease in COPD .

A recent comprehensive review of vascular disease in COPD presents several plausible mechanisms including systemic inflammation (IL-6, CRP), oxidative stress (through activation of matrix metalloproteinases), physiological stress (hypoxia, sympathetic nervous system activation), arterial stiffness, accelerated aging and protease/antiprotease inbalance. It is argued that many of these pathways are abnormal in COPD, independently predict cardiovascular disease, e.g. through atherosclerosis formation or vascular damage and also show direct pathophysiological links to the development of emphysema .

Cognitive impairment is a known consequence of cerebral small-vessel disease. Moderate to severe cognitive impairment has been shown in up to 60% of certain individuals with COPD , which may predict death and is likely to profoundly influence an individual’s ability to manage their disease . Therefore understanding the relationship between cerebrovascular disease and cognitive impairment in COPD is a research priority.

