Recruitment will be from patients attending clinic at local University Teaching Hospitals. An age-matched control group will be recruited from the Bristol Primary care Research Network North Hub, local community either through local press advertisements or University non-healthcare staff. Controls will be excluded if they have any respiratory or memory difficulties.

All Participants will be invited for an MRI, retinal photography and 2 further study visits to undergo non-invasive assessment of aortic stiffness and collect the measures outlined below. The total duration of the study should be ~ 2½ hours.

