**Healthy Ex-smoker Controls**:

Subjects must have a FEV1/FVC >70%;

Patient and control group will be matched for smoking history and age.

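### Cases come from hospital wards and clinics, controls may be advert responders or University staff, and education and deprivation are not listed for collection, so possible social confounding could not be adjusted for later

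*Protocol*

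**What the plan says.** **Source of cases.** Section 4 (Participant Entry): "Recruitment will be from inpatients and outpatient respiratory clinics at University Teaching Hospitals". The Study Design section is narrower and names no inpatients: "Recruitment will be from patients attending clinic at local University Teaching Hospitals".

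**Source of controls.** Section 4: "An age-matched control group will be recruited from the local community either through local press advertisements or University non-healthcare staff". The Study Design section adds a further source: "An age-matched control group will be recruited from the Bristol Primary care Research Network North Hub, local community either through local press advertisements". It too goes on to allow University staff. Nothing in the protocol says which of the two statements governs.

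**Matching.** Section 4.2: "Patient and control group will be matched for smoking history and age". No other matching factor is named.

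**What the protocol says about COPD patients.** Section 1.1 describes a high prevalence of cardiovascular risk factors in COPD, "including smoking, reduced physical activity and low socio-economic status".

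**What is measured.** Section 3.1 and the list of demographic and disease severity measures do not name education, occupation, deprivation or physical activity. The nearest item is a detailed medical history, whose content is not specified.

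**A control-only criterion.** Section 4: "Controls will be excluded if they have any physician-diagnosed respiratory disease or self-reported memory difficulties".

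**Analysis.** Section 7 names the t-test, the Mann-Whitney test and similar methods, with 30 cases and 25 controls.

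**The concern.** Objective 1 asks whether MRI evidence of cerebral small vessel disease in COPD is independent of smoking. Matching on smoking and age deals with those two factors. It does not deal with the other differences that arise when cases and controls come from different populations.

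People in University employment, and people who answer a press advert for a research study, may well have more education and less deprivation than patients recruited on wards and in clinics. The protocol itself says that low social status is common in COPD. If these factors are related to FA, MoCA or pulse wave velocity, part of any group difference would reflect who was recruited and not COPD. The likely direction favours the study hypothesis. For MoCA, the control-only exclusion for self-reported memory difficulties pushes the same way.

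This is a matter for the protocol. A statistical analysis plan can add covariate adjustment, but only for variables that were collected.

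**Working it through.** **1. The passages side by side**

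| Item | Study Design section | Section 4 |
| --- | --- | --- |
| Cases | clinic attenders | inpatients and outpatient respiratory clinics |
| Controls: primary care network | named | not named |
| Controls: press adverts | named | named |
| Controls: University staff | named | named |

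The two statements disagree on both groups. On either one, adverts and staff are permitted. The primary care source would weaken the concern but not remove it, because no share is fixed for any source.

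**2. The plan's own figure, as a baseline**

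The protocol gives no figure for this risk. Its one relevant calculation is power at d = 0.8 with 30 v 25, two-sided alpha 0.05, stated as above 85%.

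- Noncentrality = d × √(n1·n2/(n1+n2)) = 0.8 × √(750/55) = 2.95.
- Power is 84.0% by the normal approximation and 82.6% by the noncentral t.

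Both are slightly below the stated figure. That is a separate matter; 82.6% is used below only as the reference.

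**3. What an unmeasured imbalance could do (illustration only)**

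Assumptions, none from the protocol: no true COPD effect; the groups differ by 0.5 to 1.0 SD on education or social status; this correlates 0.1 to 0.3 with the outcome.

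Spurious d = imbalance × correlation. The rejection rate is that of the two-sided t-test with 53 degrees of freedom and noncentrality d × 3.69.

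| Imbalance (SD) | Correlation | Spurious d | False-positive rate |
| --- | --- | --- | --- |
| 0.5 | 0.1 | 0.05 | 5.4% |
| 0.5 | 0.2 | 0.10 | 6.5% |
| 1.0 | 0.2 | 0.20 | 11.2% |
| 1.0 | 0.3 | 0.30 | 19.3% |

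**4. The same question for a MoCA group comparison**

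Assumptions, again not from the protocol: 40% of the 25 controls (10 people) score 1 to 2 points higher because of education; SD 3.

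- Shift in the control mean: 0.40 × 1 = 0.4 to 0.40 × 2 = 0.8 points.
- In SD units: 0.4/3 = 0.13 to 0.8/3 = 0.27.
- False-positive rate: 7.7% to 16.2%.
- Relative to the planning effect of 0.8: 0.13/0.8 = 17% to 0.27/0.8 = 33%.

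**5. What adjustment would cost**

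With one covariate, imbalance b and group proportions 30/55 and 25/55, the covariate's R² with group is b²p/(1 + b²p), where p = (30 × 25)/55² = 0.248. The variance of the adjusted difference is multiplied by (1 − r²)/(1 − R²), where r is the covariate-outcome correlation (0 to 0.3). Residual degrees of freedom are 52.

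| Imbalance (SD) | R² | Power at d = 0.8, adjusted |
| --- | --- | --- |
| 0.5 | 0.058 | 80% to 84% |
| 1.0 | 0.199 | 74% to 78% |

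Unadjusted power is 82.6%. The calculation covers one covariate; three covariates would cost somewhat more if they are also imbalanced.

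**The case against.** **Title of the problem.** A reader might infer from section 4 that controls come only from adverts and staff and that the primary care network was dropped. The documents do not support that: the Study Design section names the network, and nothing ranks one section above the other. This objection stands. The finding is that the two statements conflict, not that the better source is absent.

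**Risk or demonstrated bias.** A reader might also infer that the FA contrast is biased. That goes too far. The protocol holds no data on education or deprivation in either group, every magnitude above is assumed, and the low end of the range is close to the nominal 5%. No figure can be given for FA. This stands.

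**Shared exclusions.** Section 4.3 excludes ischaemic heart disease, cerebrovascular disease, uncontrolled hypertension, diabetes, neurological disease, dementia and alcohol or drug abuse in all subjects. That narrows differences in vascular and brain health between the groups. It stands in part: it does not address education, deprivation or activity.

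**MoCA.** Objectives 2 to 4 concern associations within COPD, so the control source does not bear on them directly. This stands: the exposure is in objective 1 and in the group comparisons foreseen in section 7, and the MoCA figure applies only if a group comparison of MoCA is made.

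**Age.** One might argue that staff cannot provide matches for cases up to 85. But staff are one optional source, and adverts and primary care reach retired people. The age argument is not relied on.

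**Left to the analysis plan.** Adjustment may be specified there. That does not answer the point, since the protocol does not require the covariates to be collected.

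**Conclusion.** The concern holds as a risk of confounding that the protocol creates and then leaves no means of checking. Three facts carry it, all from the text: different source populations for cases and controls, matching on age and smoking only, and no listed measure of education or deprivation even though the Background identifies low social status as common in COPD.

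Its size for FA, the primary outcome, is unknown. Under the assumed imbalances and correlations the spurious difference is 0.05 to 0.30 SD, with a false-positive rate of 5.4% to 19.3%. The separate MoCA illustration gives 0.13 to 0.27 SD. These show what could happen at this sample size; they are not estimates for this study.

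The documents do not support a stronger conclusion that the staff source must be removed or that controls must be matched on four factors. With 25 controls and a 12-month recruitment window, those are debatable trade-offs and are not required. Fitness for work and physical activity may also partly result from COPD, so they should not simply be treated as confounders. The point merits a change to the protocol because the change is cheap and the data cannot be assumed to be recoverable afterwards.

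**What to change.** 1. Reconcile the Study Design section with section 4 on the sources of both cases and controls. Name the primary care research network as the preferred control source, with adverts and University staff as reserve.
2. At visit 1, record for every participant the recruitment source, years of education and a postcode deprivation score.
3. Report the FA and MoCA group contrasts unadjusted and, as a sensitivity analysis, adjusted for age, education and deprivation.

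**Cost.** A protocol amendment, two or three extra fields at visit 1 and possibly slower recruitment of controls. The adjusted contrast may lose some precision with 55 participants: for one covariate, power at d = 0.8 moves from 82.6% to 80–84% with a 0.5 SD imbalance, or to 74–78% with a 1.0 SD imbalance. Network volunteers also select themselves, so the change reduces the risk and makes it visible, but does not remove it.

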**COPD Cohort:**

Subjects with a FEV/FVC <70%

Subjects with a smoking history > 10 pack years. Ex-smokers.

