**4.3 EXCLUSION CRITERIA**

Subjects meeting any of the following criteria must not be enrolled in the study:

Resting oxygen saturations <92% on room air.

Long term oxygen therapy

Recent exacerbation of COPD (4 weeks)

Ischaemic heart disease

Cerebrovascular disease

Uncontrolled hypertension

Diabetes mellitus

Hepatic failure

Neurological disease

Non-cured tumours

Obstructive sleep apnoea

Current of past alcohol/drug abuse

Known history of dementia

Visual or hearing impairment that precludes neuropsychological assessment

Neuropsychological tests undertaken outside the study

Pregnant women or women who are lactating

Known alpha 1 anti-trypsin deficiency as a cause of their COPD

History of psychiatric disorders, or other conditions that will impact on the validity of their consent or interfere with compliance to perform study procedures.

Contra indication to MRI scanning

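### Controls, but not COPD cases, are excluded for memory difficulties, which tilts the case-control contrasts on MoCA and, indirectly, on fractional anisotropy towards the hypothesis

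*Protocol*

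**What the plan says.** The control-only rule appears twice.

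- Protocol section 4 (Participant Entry): "Controls will be excluded if they have any physician-diagnosed respiratory disease or self-reported memory difficulties".
- Protocol section 3 (Study Design): "Controls will be excluded if they have any respiratory or memory difficulties".

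The COPD cohort criteria under section 4.2 are an airflow ratio and "Subjects with a smoking history > 10 pack years. Ex-smokers". They contain no memory criterion.

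Section 4.3 applies to everyone ("Subjects meeting any of the following criteria must not be enrolled in the study"). Its nearest cognitive item is "Known history of dementia". It also lists neurological disease, cerebrovascular disease, alcohol or drug abuse, psychiatric disorders that affect consent or compliance, and neuropsychological testing done outside the study. Self-reported memory difficulty is not on the list.

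On comparability, section 4.2 says "Patient and control group will be matched for smoking history and age". Section 3.1 makes FA the primary outcome and MoCA a secondary one. Section 1.1 describes cognitive impairment as a recognised result of cerebral small-vessel disease.

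**The concern.** A case-control contrast needs entry rules that treat both groups alike, apart from the rule that defines the disease. Excluding controls with respiratory disease is part of that definition. Excluding controls with memory difficulties is not, and the protocol gives no reason for it.

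Take two ex-smokers of the same age and smoking history, each mildly forgetful and never formally assessed. The one with COPD may enter and the one without may not. On the protocol's own account of how small-vessel disease affects cognition, the people removed from the control group will tend to have lower MoCA scores and somewhat more white-matter damage. The controls then look healthier than the population they stand for, and part of any observed difference comes from the entry rule.

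Matching on age and smoking history does not correct this, nor do the tests named in section 7 (t-test or Mann-Whitney). Controls who were turned away cannot be recovered at analysis.

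**Working it through.** **Figures from the plan.** The protocol gives no figure for this selection effect. Its yardstick is section 7: 30 cases v 25 controls, d = 0.8, two-sided alpha 0.05, power stated as above 85%. Recomputed power is 84.0% by the normal approximation and 82.6% by the exact noncentral t with 53 degrees of freedom. The small shortfall is a separate matter. Here only the group sizes and the 0.8 SD design effect are used.

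**Assumptions, not in the documents.**
- p, the share of otherwise eligible controls who report memory difficulty: 20-40%.
- r, the correlation between the underlying tendency to report difficulty and the outcome: 0.2-0.4.
- That tendency and the outcome are jointly normal, and there is no true COPD effect.

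**Shift in the control mean.** Removing the worst fraction p on the underlying tendency raises the retained controls' mean outcome, in SD units, by

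shift = r × φ(z) / (1 − p), where z is the 1 − p quantile of the standard normal.

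- p = 0.20: z = 0.842, φ(z) = 0.280, so the multiplier is 0.280 / 0.80 = 0.350.
- p = 0.40: z = 0.253, φ(z) = 0.386, so the multiplier is 0.386 / 0.60 = 0.644.

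**False-positive rate.** The standard error of the difference, in SD units, is √(1/30 + 1/25) = 0.271. The noncentrality is shift / 0.271, and the two-sided rejection probability comes from the noncentral t with 53 degrees of freedom.

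| p | r | Shift (SD) | Noncentrality | Rejection rate |
|---|---|---|---|---|
| 20% | 0.2 | 0.070 | 0.26 | 5.7% |
| 20% | 0.4 | 0.140 | 0.52 | 8.0% |
| 40% | 0.2 | 0.129 | 0.48 | 7.5% |
| 40% | 0.4 | 0.258 | 0.95 | 15.4% |

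**Wider range.** With p = 10-40% and r = 0.1-0.5, simulation of 100,000 studies per setting gives shifts of 0.02-0.32 SD and rejection rates of 5.1-22.3%. A middle case (p = 20%, r = 0.3) gives 0.105 SD and 6.6%.

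**Against the design effect.** 0.070 / 0.8 is about 9% of the effect the study is sized for, and 0.258 / 0.8 is about 32%.

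**Which contrasts are touched.** Objective 1 compares MRI measures between groups, so FA is affected, but through a chain: reported difficulty, then cognition, then small-vessel disease, then FA. The documents support the link between small-vessel disease and cognition and say nothing on how self-report relates to FA, so r for FA is likely to be at or below the low end. MoCA is closer to the screening question, so any group comparison on it is affected more directly. Objectives 2 to 4 concern associations within COPD, and a rule that acts only on controls cannot bias them.

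**The case against.** **The shared exclusions narrow the gap.** Section 4.3 removes dementia, neurological and cerebrovascular disease and, read literally, anyone tested neuropsychologically elsewhere, from both groups. This stands. A reader might infer that dementia is the only cognitive safeguard on cases, but it is not. The asymmetry is confined to milder complaints that have not been formally assessed.

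**No MoCA contrast is specified.** Objective 4 concerns cognition within COPD, and section 7 names group differences in brain pathology and vascular function. This also stands, so the point applies to any MoCA contrast that is made. MoCA is still a listed secondary outcome in a two-group study, and such a comparison would be natural.

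**FA is not itself screened, and the size is assumed.** Both are correct. It would go too far to say that controls are screened on the primary outcome. The direction follows from the protocol's own reasoning, but the magnitude does not.

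**Selection on education.** A reader might add that some controls are to be "recruited from the local community either through local press advertisements or University non-healthcare staff", while section 1.1 lists "traditional cardiovascular risk factors in patients with COPD including smoking, reduced physical activity and low socio-economic status", and conclude that controls are better educated and that MoCA needs an education covariate. The documents do not support this. They do not state the role or education of the staff, they name other recruitment sources, and they mention socio-economic status as a cardiovascular risk factor. Covariates are commonly left to an analysis plan, which is not shown here.

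**Small study.** With 55 participants and the aim of supporting later funding, a modest bias may seem tolerable. This bears on severity, not on whether the rule should stay, since removing it costs almost nothing.

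**Conclusion.** The concern holds in this limited form. The control-only memory exclusion is explicit, stated twice and unexplained, and it biases the Objective 1 contrast on FA, and any group contrast on MoCA, towards the hypothesis. Under the stated assumptions (20-40% of controls reporting difficulty, correlation 0.2-0.4) the spurious difference is 0.07-0.26 SD and the false-positive rate is about 6-15% instead of 5%. FA is probably at or below the low end, where the effect is small. Confidence is high that the asymmetry exists and in its direction, and low in its size. It should be corrected because it cannot be repaired once controls have been turned away. It does not by itself invalidate the primary comparison and does not rank among the must-fix defects.

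**What to change.** - Delete the memory clause from the control-only sentences in sections 3 and 4, so that the section 4.3 exclusions are the common cognitive criteria for both groups. The two sentences also differ in how they word the respiratory exclusion and should be aligned in the same edit.
- Record self-reported memory difficulty in both groups at Visit 1, so that its frequency can be reported by group.

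With the same rule in both groups, the selection shift under no true effect is zero and the error rate returns to 5%. The sample size does not change. The cost is wording in two places and one interview question. Control MoCA and FA may be slightly more variable: in the model above, the rule cuts the control SD by at most about 5% (p = 40%, r = 0.4), and that reduction would be given up.

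Applying the exclusion to COPD cases as well would also restore symmetry but is not recommended. Section 1.1 cites moderate to severe cognitive impairment in up to 60% of some COPD patients, so the rule could remove many eligible cases and narrow the cognitive range that Objective 4 needs.
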